## Objectives {7}

The aim of the study is to focus on depression and anxiety symptoms of individuals of working age and to expand the scope to cover exhaustion as well. This RCT’s intervention is targeted at adult individuals who are in employment, in their studies, temporarily unemployed, on short-term sick leave or rehabilitation allowance and have one or various of the following disorders or conditions: depression, anxiety, work-related stress or exhaustion.

Objective 1: To examine whether IIMT, offered in four different modifications, improves the participants’ condition relative to the control/TAU (Treatment as usual) group. We also aim to find out whether any of the modifications of the IIMT are more effective than plain IIMT.

Objective 2: To understand whether certain musical responsiveness or personality profile explains a client’s improvement in music therapy.

Objective 3: To increase the understanding of the dynamics of therapeutic change by IIMT in its original form and with selected modifications.

Objective 4: To increase the understanding of the essence, mechanisms and trajectories of work-related stress and burnout and their relationship to depression and anxiety.

Hypothesis 1: All the experiment groups (ML + IIMT, VAT + IIMT, VAT + ML + IIMT) improve significantly relative to the control/TAU group.

Hypothesis 2: ML + IIMT group improves significantly better than the IIMT only group.

Hypothesis 3: VAT + IIMT group improves significantly better than the IIMT only group.

Hypothesis 4: VAT + ML + IIMT group improves significantly better than ML + IIMT, and VAT + IIMT groups.

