#### Sample size {14}

We will recruit 200 working-age adults (18–65 years of age) suffering from one or several of the following disorders: depression (ICD-10: F32 or F33), anxiety (ICD-10: F41), or exhaustion. The sample of participants will be randomised into four groups (50 + 50 + 50 + 50) of which two groups (*n* = 100) will receive vibroacoustic treatment (VAT) and two groups (*n* = 100) not whereas two groups (*n* = 100) will receive music listening (ML) and two groups (*n* = 100) not (see Table 2).

**Table 2 Tab2:** Factorial design

	VAT yes	VAT no	
ML yes	50	50	*n* = 100
ML no	50	50	*n* = 100
	*n* = 100	*n* = 100	

For each condition, the selected sample size provided a statistical power of 0.985 for detecting a medium standardised effect size of Cohen’s d = 0.5 in a mixed-model analysis [47], with a 2-tailed significance level of *p* < 0.05 and intra-participant correlation of ρ = 0.6. For the comparison between IIMT only vs waiting-list control, the selected sample size provided statistical power of 0.9 for detecting a medium effect size (d = 0.23) in a repeated measures t-test, with a 2-tailed significance level of *p* < 0.05. These high-power levels ensure a robust detection of clinically meaningful effects, even after accounting for potential participant dropouts, while reducing the likelihood of Type II errors. Also, the selected sample sizes also retain adequate power (> 0.8) to detect smaller effects (e.g., d = 0.2), thus providing sensitivity to subtle group differences.

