## Statistical methods

### Statistical methods for primary and secondary outcomes {20a}

All statistical tests will be two-tailed with a significance level of 5%, and no adjustments will be made for multiplicity. Primary and secondary outcome measures at baseline, post-intervention, and at the first and second follow-ups will be treated as continuous dependent variables.

For the IIMT group, which also serves as the waiting-list control, we will assess clinical improvement by comparing their progress during the intervention period with that observed during the waiting period prior to treatment. Specifically, we will perform paired samples t-tests for each outcome measure, comparing the change from baseline 2 (6 weeks; pre-intervention) to post-intervention (12 weeks) against the change from baseline 1 (0 weeks; no intervention) to baseline 2 (6 weeks). Prior to analysis, we will assess the normality of the difference scores to ensure the assumptions of the t-test are met. This comparison will help isolate the treatment effect from natural fluctuations over time.

Since the participants are randomised either to the waiting list plus plain IIMT group or to one of the other three arms (B, C, and D), comparisons between plain IIMT and the waiting list are based on within-subject analyses rather than fully randomised group contrasts. No direct comparisons between the waiting list group and arms B, C, and D will be performed.

To evaluate the effects of VAT and ML on these outcomes, repeated-measures linear mixed-effects models will be applied [50]. A key advantage of this design is its ability to retain participants with missing data, ensuring that all participants contribute to the analysis. Additionally, they can account for baseline group differences, to avoid overestimating the effect size of treatment. VAT and ML will be included as fixed effects, with a random intercept for each participant to account for the dependency of repeated measurements. To control for baseline differences across conditions, treatment terms will be omitted from the model, allowing the effects of VAT and ML to be estimated through their interactions with time. As an exploratory analysis, the models will be extended to include a VAT × ML interaction term to examine potential synergistic effects between the two interventions.

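### Hypotheses 2 to 4 are differences between single arms, but the only non-exploratory analyses of VAT and ML are factor margins, which match them only if the two elements do not interact

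*Protocol article*

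**What the plan says.** Objectives {7} words the three hypotheses as comparisons of named arms:

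- "Hypothesis 2: ML + IIMT group improves significantly better than the IIMT only group" (B − A).
- "Hypothesis 3: VAT + IIMT group improves significantly better than the IIMT only group" (C − A).
- "Hypothesis 4: VAT + ML + IIMT group improves significantly better than ML + IIMT, and VAT + IIMT groups" (D − B and D − C).

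Sample size {14} puts 50 participants in each arm, so each margin of the 2 × 2 table holds 100. It then states: "For each condition, the selected sample size provided a statistical power of 0.985", for d = 0.5, two-sided 5% and a within-participant correlation of 0.6.

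The statistical methods section {20a} estimates VAT and ML through their interactions with time, with treatment terms left out so that all arms share a baseline. The overall effect is defined for having against not having each factor, and the responder tests are run once for VAT and once for ML. The two factors are considered jointly only here: "As an exploratory analysis, the models will be extended to include a VAT × ML interaction term to examine potential synergistic effects". No B − A, C − A, D − B or D − C contrast is described.

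**The concern.** A factor margin averages two arm differences. The ML margin averages B − A (ML without VAT) and D − C (ML on top of VAT). The VAT margin averages C − A and D − B. Hypothesis 2 concerns only the first half of the ML average, and Hypothesis 4 concerns the second half of both averages. One number stands for both halves only when they are equal, that is, when VAT and ML do not interact.

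The article does not state that assumption, and its intervention description gives reason to doubt it. The added component is about 15 minutes in B, in C and in D alike, so D fits both elements into the time that B and C give to one. An effect in D well short of the sum of the two is plausible.

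What is at stake is which claim the trial may make. A significant margin could be reported as support for a pairwise hypothesis that it does not test, in either direction: D may add nothing to B or C, or all the benefit may lie in D while B and C equal A.

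**Working it through.** **Inputs.** 50 per arm, 100 per margin, d = 0.5, ρ = 0.6, two-sided 5% (Sample size {14}); three post-baseline visits and a common baseline (statistical methods {20a}). Assumed here: SD = 1, compound symmetry, the same effect at all three visits, no dropout. Positive values mean improvement.

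**1. Algebra.** Let I = D − B − C + A.

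- ML margin = ½[(B − A) + (D − C)], so B − A = ML margin − I/2 and D − C = ML margin + I/2.
- VAT margin = ½[(C − A) + (D − B)], so C − A = VAT margin − I/2 and D − B = VAT margin + I/2.

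Margin and arm contrast agree only if I = 0.

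**2. Reproducing 0.985.** The mean of three post-baseline values has variance (1 + 2 × 0.6)/3 = 0.7333, SD 0.8563. For 100 v 100, SE = 0.8563 × √(2/100) = 0.1211 and power = Φ(0.5/0.1211 − 1.96) = 0.985. The stated figure therefore reproduces as a margin without baseline adjustment.

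**3. Power for the arm contrasts (50 v 50, d = 0.5).** With a common baseline the variance of the three-visit mean falls to 0.7333 − 0.6² = 0.3733, SD 0.611. D − B and D − C share arm D, so their estimates correlate 0.5.

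| | SE | Power per pair | Both H4 contrasts |
|---|---|---|---|
| Unadjusted (SD 0.8563) | 0.1713 | 0.83 | 0.73 |
| Common baseline (SD 0.611) | 0.1222 | 0.98 | 0.97 |

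**4. A case where Hypothesis 4 is false.** Let A = 0 and B = C = D = 0.5. Then D − B = D − C = 0, I = −0.5, and each margin is 0.25.

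- Unadjusted: Φ(0.25/0.1211 − 1.96) = 0.542 per margin.
- Common baseline: SE = 0.611 × √(2/100) = 0.0864, and Φ(0.25/0.0864 − 1.96) = 0.825 per margin.

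The two margin estimates are uncorrelated in this balanced layout, so both are significant with probability 0.542² = 0.29 to 0.825² = 0.68. With a common effect of 0.8 SD (margins 0.4), the range is 0.83 to 0.99. Tested directly, D − B and D − C would both favour D in about 0.5% of such trials.

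**5. The mirror case.** Let A = B = C = 0 and D = 1. Each margin is 0.5, and both are significant in 0.985² = 0.97 of trials (unadjusted), although Hypotheses 2 and 3 are false.

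**6. Whether the exploratory interaction settles it.** The unadjusted SE of I is 0.8563 × √(4/50) = 0.2422, so I = −0.5 is detected with probability 0.54 (0.82 with a common baseline). In 13.5% of unadjusted trials both margins are significant and the interaction is not. Nor is the interaction a test of Hypothesis 4: with additive effects (0, 0.5, 0.5, 1.0), Hypothesis 4 is true and I = 0.

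**The case against.** The trial is declared a 2 × 2 factorial, its design table shows margins of 100, and margins are the conventional primary analysis of such a design. That stands as a defence of the analysis. It does not make the analysis a test of the hypotheses as worded, and it holds for them only under no interaction. Nor is this a detail left to an analysis plan: the article fixes its model, its effect definition and its responder test, all on the margins.

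Three stronger readings are tempting, and the article does not support them.

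- *The plan would declare Hypothesis 4 proven from two significant margins.* It contains no such rule. It assigns Hypothesis 4 no test, and the 29% to 68% is the chance that a reader could draw the wrong inference.
- *The arm contrasts are underpowered.* The 0.83 and 0.73 ignore baseline. The common-baseline model that the article describes gives 0.98 and 0.97 under the same ρ. The 50 v 50 figure of 0.9835 also lies close to the stated 0.985, so the 100 v 100 origin is a good match but not proven.
- *The interaction term omits time and so cannot measure synergy.* That is the literal wording. But the preceding sentence says effects are estimated through interactions with time, and a condensed article may well intend the same for VAT × ML. It needs clarifying, and the point does not depend on it.

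**Conclusion.** The point holds as a mismatch between hypotheses and analysis. As written, no non-exploratory analysis tests Hypotheses 2 to 4 unless VAT and ML are additive, and Hypothesis 4 has no test. The size depends on the true pattern. With no interaction there is no harm. With B, C and D equal at 0.5 SD above A, both margins are significant in 29% (unadjusted) to 68% (common baseline) of trials although Hypothesis 4 is false. The problem is what is being estimated; a shortage of participants is not shown. The figures rest on ρ = 0.6, compound symmetry, equal effects at the three visits and no dropout.

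**What to change.** Choose one of two routes.

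1. Keep the hypotheses. Fit VAT × time, ML × time and VAT × ML × time, stating that the interaction is crossed with time. Test Hypothesis 2 as B − A, Hypothesis 3 as C − A, and Hypothesis 4 as D − B and D − C with both required. Use one pre-named summary, such as the mean of the three post-baseline visits. The margins become supportive.
2. Keep the margins. Reword Hypotheses 2 to 4 as main effects of ML and VAT, and state the no-interaction assumption.

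In either case, say that 0.985 reproduces as the 100 v 100 margin without baseline adjustment. Under route 1, also give both pairs of power figures from step 3 with the assumption behind each.

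The cost is wording and, under route 1, three more model terms (one per post-baseline visit). Stated power is somewhat lower than for the margins: on the common-baseline model, 0.98 per pair against more than 0.99. No participants are added, and recruitment is expected to run to the end of December 2028, so the change can be made before the data are complete.

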In addition to evaluating treatment effects post-intervention and at follow-up time points, we will calculate an overall treatment effect over time (denoted as *B*). This will represent the raw mean difference associated with the presence versus absence of each factor. *B* will be derived by summing the regression coefficients corresponding to each condition across all time points [28]. To estimate effect sizes for each outcome, the overall treatment effect over time will be divided by the baseline standard deviation of the respective measure across all participants.

For each participant, a dichotomous treatment response variable will be calculated, defined as a reduction of at least 50% in CORE-OM scores between the baseline and post-intervention assessments. Fisher’s exact test and odds ratios will be calculated separately for VAT and ML. For statistically significant effects, clinical significance will be assessed by calculating the risk difference and the number needed to treat (NNT).

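### The overall effect B is a sum of visit-specific coefficients but is called a mean difference, so the standardised effect sizes come out about three times too large

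*Protocol article*

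**What the plan says.** All of this stands in the protocol article, in Statistical methods for primary and secondary outcomes {20a}, except the planning figures.

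- **Outcomes in the model:** "Primary and secondary outcome measures at baseline, post-intervention, and at the first and second follow-ups will be treated as continuous dependent variables". That is one baseline visit and three post-baseline visits.
- **How the factors enter:** "treatment terms will be omitted from the model, allowing the effects of VAT and ML to be estimated through their interactions with time".
- **Visit-specific effects:** B is reported "In addition to evaluating treatment effects post-intervention and at follow-up time points", so effects are estimated separately at each visit.
- **Meaning given to B:** "This will represent the raw mean difference associated with the presence versus absence of each factor".
- **Derivation of B:** it "will be derived by summing the regression coefficients corresponding to each condition across all time points", with a citation to an earlier trial from the same unit.
- **Effect size for each outcome:** "the overall treatment effect over time will be divided by the baseline standard deviation of the respective measure across all participants".
- **Planning, in Sample size {14}:** "a statistical power of 0.985 for detecting a medium standardised effect size of Cohen’s d = 0.5 in a mixed-model analysis", "with a 2-tailed significance level of *p* < 0.05 and intra-participant correlation of ρ = 0.6".

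The article nowhere divides or weights the sum by the number of visits.

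**The concern.** Two adjacent sentences define B in incompatible ways. A mean difference between factor present and factor absent is on the scale of one measurement of the outcome. A sum of three such differences is not. Dividing the sum by a baseline standard deviation, which is the spread of a single measurement, produces a number that looks like a standardised mean difference but is about three times as large.

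B divided by the SD is the only effect size the article defines for the mixed-model analyses, and it applies to the primary outcome (CORE-OM) and every secondary outcome. A reader or meta-analyst would naturally set it against the planning value of d = 0.5. An effect of 0.2 SD, which Sample size {14} treats as small, would appear as 0.6, above the value that section calls medium.

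**Working it through.** **Inputs.** Three post-baseline visits and no treatment main terms ({20a}); 100 versus 100 participants per factor, d = 0.5, within-participant correlation 0.6, two-sided 5% ({14}).

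**1. The plan's own power figure.** Take d as the difference in the average of three post-baseline measurements, in SD units.

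- Variance of the average of m measurements: (1 + (m − 1)ρ)/m = (1 + 2 × 0.6)/3 = 0.733
- SE of the difference: √(2 × 0.733/100) = 0.1211
- z = 0.5/0.1211 = 4.13
- Power = Φ(4.13 − 1.96) = 0.985

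This is the stated figure. If 0.5 were on the summed scale, the average would be 0.5/3 = 0.167, z = 0.167/0.1211 = 1.38, and power = Φ(1.38 − 1.96) = 0.28. The match supports a planning value on the averaged scale but is not unique. At 100 versus 100, two measurements give 0.977 and four give 0.988. At 50 versus 50, three measurements with baseline adjustment give 0.983.

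**2. What the coefficients are.** With time dummy-coded against baseline and no treatment main term, the modelled difference for a factor is zero at baseline and b_post, b_6m and b_12m at the later visits. Each coefficient is the mean difference at its visit, so

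- sum = b_post + b_6m + b_12m = 3 × average
- constant 0.2 SD: sum 0.6, average 0.2
- constant 0.3 SD: sum 0.9, average 0.3

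**3. Simulation check.** A random-intercept model without treatment main terms was fitted to simulated data (one data set per pattern, 4,000 participants, correlation 0.6, SD 1).

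| True effect at post / 6 m / 12 m | Sum/SD | Average/SD | Sum under successive-step coding (raw) |
|---|---|---|---|
| −0.5 / −0.5 / −0.5 | −1.53 | −0.51 | −0.50 |
| −0.6 / −0.5 / −0.4 | −1.50 | −0.50 | −0.42 |
| −0.6 / −0.3 / 0 | −0.99 | −0.33 | −0.02 |

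**4. Other codings.** Under successive-step coding the coefficients telescope. For −0.6 / −0.5 / −0.4 the steps are −0.6, +0.1 and +0.1, and they sum to −0.4, the 12-month effect, while the average is −0.5. That sum equals the average only when the two happen to coincide, as they do for a constant effect. With linear time there is a single slope per factor and nothing to sum.

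**5. Inference.** Multiplying the contrast by 3 multiplies its SE by 3. The test statistic and p-value do not change; the estimate and both confidence limits are tripled.

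**The case against.** The strongest reply is that the factor of three is inferred. The article does not state how time is coded, and it cites an earlier trial for the method. That source was not available, and the trial's code may in fact average. The target quantity, a mean difference, is named correctly, so the fault may lie only in how its derivation is described. The damage is also bounded: visit-specific differences are reported alongside B; the responder odds ratios, risk differences and number needed to treat do not use it; nor do the paired t-tests in the waiting-list group. No significance decision changes. The article also never calls B divided by the SD Cohen's d, and the power match is not unique.

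Much of this stands as a limit on scope. The exact factor of three is conditional on categorical time against baseline, although visit-specific effects with omitted treatment terms make that the natural reading. The power match is support only, and the finding does not need it. But the contradiction remains. If the code sums, the reported effect sizes are wrong; if it averages, the text is wrong. Nor can this be put down to detail left for an analysis plan, because the article itself fixes the formula.

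**Conclusion.** The definition is wrong as written. Under categorical time with baseline as reference, the sum over three post-baseline visits is exactly three times the time-averaged mean difference, and so are the standardised effect size and its confidence limits for the primary and all secondary outcomes. Under successive-step coding the sum is instead the 12-month effect alone. Neither is generally the mean difference over time that the article says B represents. The error concerns magnitude and interpretation, not testing. It is confined to B and the effect sizes derived from it.

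**What to change.** Replace the summing rule with B = (b_post + b_6m + b_12m)/3 for each factor, estimated as one linear contrast from the mixed model with its own SE and confidence interval, and divide that by the baseline SD. State that time is categorical with baseline as reference, so that the coefficients are unambiguous. If the investigators prefer to keep a cumulative sum, they should call it that, drop the description as a mean difference, and not present its ratio to the SD as a standardised mean difference. The average is the better choice because it is on the scale on which the 0.985 power reproduces.

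The cost is one sentence and one divisor in the code. No interim analysis is planned ({21b}) and recruitment is expected to run to the end of December 2028 (Trial status), so the change can be made before any comparative analysis. It does not affect conduct, sample size or any p-value.

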### Methods for additional analyses (e.g. subgroup analysis) {20b}

In addition to the primary efficacy analysis, an adjusted efficacy analysis and two sensitivity analyses will be conducted. Each repeated-measures linear mixed-effects model for continuous outcomes will be adjusted for the following prognostic covariates: age group (18–34, 35–49, 50–65), gender, medication use (antidepressants, anxiolytics, or hypnotics). Therapists will be added as random effects. Model fit will be assessed through the Akaike Information Criterion (AIC) and Bayesian Information Criterion (BIC). The covariates that optimise these criteria will be retained in the final model. Two sensitivity analyses will be performed for the primary outcome: (1) a single imputation method using Last Observation Carried Forward (LOCF), which assumes no change for missing data, and (2) an analysis based on treatment as received.

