### Methods in analysis to handle protocol non-adherence and any statistical methods to handle missing data {20c}

An intention-to-treat (ITT) approach will be employed, incorporating all available data regardless of whether the treatment was received as intended. Participants who discontinue the study before completing the intervention will be classified as dropouts.

For dichotomous variables (e.g., early study termination, treatment response), missing data will be imputed using a conservative approach in which participants who leave the study early will be assumed to have experienced a negative outcome (i.e., dropout or no response).

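### Fisher's exact test for CORE-OM response, run once per factor at 100 v 100, is valid but conservative and gives up about 4 to 6 points of power

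*Protocol article*

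**What the plan says.** All references are to the protocol article.

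- **Response variable** ({20a}): a yes/no variable per participant, "defined as a reduction of at least 50% in CORE-OM scores between the baseline and post-intervention assessments".
- **Test** ({20a}): Fisher's exact test, and "odds ratios will be calculated separately for VAT and ML". No response model containing both factors or the baseline score is described. The next sentence calculates the risk difference and number needed to treat (NNT) only where the effect is significant.
- **Level** ({20a}): "All statistical tests will be two-tailed with a significance level of 5%, and no adjustments will be made for multiplicity".
- **Covariates** ({20b}): "Each repeated-measures linear mixed-effects model for continuous outcomes will be adjusted for the following prognostic covariates". This covers the continuous outcomes and does not reach the response analysis.
- **Numbers** (Sample size {14} and Table 2): participants are "randomised into four groups (50 + 50 + 50 + 50"), so each level of VAT and of ML has 100.
- **Missing response** ({20c}): "participants who leave the study early will be assumed to have experienced a negative outcome". The denominators therefore stay at about 100 per level.

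**The concern.** Fisher's test conditions on both margins of the 2 x 2 table. Its p-values are discrete, so the chance of rejecting a true null lies below the nominal level. This protection is useful in sparse tables. With 100 per level and response rates that are not extreme, it is not needed, and it costs power.

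The cost falls on the only responder analysis in the plan, and there it also acts as a gate: an effect that misses 5% gets no risk difference and no NNT. Those absolute measures are what a clinical reader would look for, given that Trial design {8} aims at clinical as well as statistical superiority.

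**Working it through.** **1. The plan's own power figure.** The plan gives no power for response. Its figure for the continuous mixed model is 0.985 for d = 0.5 with ρ = 0.6. Taking the mean of three post-baseline visits under compound symmetry, the SD factor is √((1 + 2 × 0.6)/3) = 0.856. The noncentrality is (0.5/0.856) × √(100/2) = 4.129, and Φ(4.129 − 1.960) = 0.985. This reproduces and confirms 100 v 100 per factor. It says nothing about the response test.

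**2. Real size, 100 v 100.** Let A and B be independent Binomial(100, p). Size is the sum of P(A = a)·P(B = b) over all 101 × 101 tables that the test rejects at two-sided 5%. The rates p are assumptions, since the plan gives none.

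| Response rate | Fisher | Mid-p | Chi-square, uncorrected |
|---|---|---|---|
| 5% | 2.1% | 3.6% | 4.4% |
| 10% | 2.9% | 4.5% | 5.2% |
| 20% | 3.3% | 4.8% | 5.1% |
| 30% | 3.5% | 4.9% | 5.1% |
| 40% | 3.6% | 5.1% | 5.1% |
| 50% | 4.0% | 5.6% | 5.6% |

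**3. Power, same enumeration with unequal rates.**

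| Rates | Fisher | Chi-square | Difference (points) |
|---|---|---|---|
| 10% v 25% | 0.762 | 0.816 | 5.4 |
| 20% v 35% | 0.608 | 0.666 | 5.9 |
| 20% v 40% | 0.845 | 0.880 | 3.5 |
| 30% v 45% | 0.535 | 0.594 | 6.0 |
| 30% v 50% | 0.792 | 0.832 | 4.0 |

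The result does not hinge on exactly 100 per level. At 80 per level and 30% v 45% the figures are 0.437 and 0.498.

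**4. What the gate does.** Suppose 30/100 v 44/100 respond. The pooled rate is 74/200 = 0.37, the standard error is √(0.37 × 0.63 × 0.02) = 0.0683, z = 0.14/0.0683 = 2.05, and chi-square p = 0.040. The two-sided hypergeometric sum for the same table gives Fisher p = 0.057. Under the plan, this 14-point difference (NNT 1/0.14 ≈ 7) would not be calculated.

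**5. What covariates add.** In a simulation of 4 × 50 participants (6,000 runs), the test was a likelihood-ratio test for VAT in a logistic regression on VAT, ML and baseline. Assumptions not in the document: baseline CORE-OM mean 1.8 and SD 0.6, mean fall 0.6, follow-up SD 0.8 to 1.2 times baseline.

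- At the plan's ρ = 0.6, size was 5.1% to 5.3%. In a typical scenario (27% v 43%) power was 0.605 for Fisher, 0.659 for chi-square and 0.670 for the model. About 5.5 of the 6.5 points gained come from dropping Fisher and about 1 from the covariates.
- With equal SDs, baseline is then almost unrelated to a 50% relative fall (correlation about −0.09), because it is already in the definition of response.
- At an assumed ρ = 0.8 the covariates add more, about 5 to 9 points depending on the other assumptions.

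**6. Adding every stratification factor.** A further simulation (5,000 runs) used 3 age groups, 2 genders, 5 employment and 3 health categories, assumed to have no prognostic effect. The likelihood-ratio test had size 5.7% to 6.1%. Power was 0.607 and 0.832 at 30% v 45% and 30% v 50%, against 0.599 and 0.835 for plain chi-square.

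**The case against.** The strongest reply is that nothing here is wrong. Fisher's test is valid and keeps the error rate at or below 5%. In a plan without multiplicity adjustment, mild conservatism harms no error control. The primary outcome is tested as a continuous variable by mixed models, and the stated power belongs to those models, so no design figure changes. All of this stands, and it sets the severity.

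Three stronger readings are tempting, and the document does not support them:

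- **That separate odds ratios for VAT and ML are biased because each ignores the other factor.** In the balanced 2 x 2 layout of Table 2, comparing 100 v 100 at the margins is a standard, randomisation-valid factorial contrast. A covariate-adjusted odds ratio is a different (conditional) quantity, not a correction of this one.
- **That leaving out baseline CORE-OM costs much power.** At the plan's own ρ of 0.6 it and the other factor are worth about 1 point together.
- **That the power is lost for nothing.** Fisher buys a guarantee that the alternatives lack. At 100 per level that guarantee is of little use, but it is not nothing.

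It can also be said that a less conservative test leaves the significance gate in place. That is true, so the fix below reports the risk difference whatever the p-value.

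**Conclusion.** The point holds as a cheap improvement of minor severity. The stated test runs at about 2% to 4% instead of 5%, and it loses about 4 to 6 points of power against an uncorrected chi-square test. This occurs in a supporting analysis whose significance determines whether absolute effects are calculated.

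The size and power figures are exact for 100 per level but depend on assumed response rates. Fisher stayed below 5% at every rate tried. The covariate figures come from simulation and depend on assumed CORE-OM moments and on ρ. The case for a joint model is therefore mainly consistency with the mixed model, which fits VAT and ML together and allows for baseline.

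**What to change.** In {20a}, replace the two Fisher tests with one logistic regression of response on VAT, ML and baseline CORE-OM. At minimum, use an uncorrected chi-square or mid-p test for each factor. Report odds ratios and marginal (standardised) risk differences with 95% confidence intervals for both factors, whether or not they reach significance. Keep Fisher's test as the fallback for sparse data.

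Do not require all the stratification factors in the model: with many levels they push the likelihood-ratio test slightly above 5% for no gain in power.

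The cost is a sentence or two of analysis text, since every variable is already collected. The statistical price is the loss of the guarantee of size at or below 5%, with chi-square and mid-p reaching about 5.6% near a 50% response rate.
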